### Data collection

Data during the CHAP intervention session will be collected either on paper or through an electronic form. All data collected will be protected and kept confidential. Paper forms will be kept in locked cabinets in the research office. All data in the electronic platform will be kept in encrypted and firewall-protected servers only accessible to the research team, volunteers, and nurses implementing the program. All data analysis of collected data will be anonymized.

The primary outcomes will be assessed using de-identified administrative datasets in Ontario and Quebec. We will use building-level data for each of these outcomes, at monthly intervals for 1 year prior to and for the 1-year duration of the program.

Quality of life data will be collected using the EQ-5D-5 L, administered by a research assistant or volunteer to all residents of intervention buildings who attend a CHAP session. This will be done at two time points, when the participants attend their first CHAP session and then at the final CHAP session. Cost-effectiveness will be calculated by collection of program cost data and health outcomes. Health experiences and perceptions of participants will be collected at the end of the study by a trained research assistant using four qualitative focus groups of intervention residents, including two in Ontario and two in Quebec.

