### Data analysis plan

#### Quantitative data

We will analyze data with the building or cluster as the primary unit of analysis, rather than the individual. The reason is that it is not possible to acquire individual-level consent from the control building residents to obtain their health administrative data. It is possible to get this information in aggregate form for each building.

The analysis and reporting of the trial will follow the Consolidated Standards of Reporting Trials (CONSORT) extension to cluster trials [26]. The analysis of the baseline characteristics will be based on descriptive statistics reported as count (percent) for categorical variables and mean (SD) or median (first quartile, third quartile) for continuous variables. The analysis of primary and secondary outcomes will follow the intention-to-treat principle. For the primary building-level outcome measure we will analyze the data using analysis of covariance (ANCOVA), adjusting for pairing (fixed-effect) and baseline rate (covariate) in the model. For the secondary individual-level data (quality of life, QALY), we will use the intention-to-treat principle analysis and analyze the data using generalized estimating equations (GEEs) assuming an exchangeable correlation structure to adjust for clustering within a building [27]. Multiple imputation (iterative Markov chain Monte Carlo method) with five imputations will be used if more than 5% of the participant outcome data is missing in the follow-up survey [28]. All analyses will be performed using STATA 11.2.

Since CHAP is a health promotion program that can be integrated into the health system and is expected to impact health system utilization, we will conduct a cost-effectiveness analysis. This analysis will be conducted at a building level and will therefore be based on administrative data and program costs. Therefore, the sample size will be the same as that for the main outcome.

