### Control of bias and loss to follow-up

This will be an open trial with no blinding or masking. Due to the nature of the health intervention (health sessions in intervention buildings), it will not be possible to blind participants as to whether they are receiving the intervention or not. However, since randomization is at the building level and the primary outcome (ED visit rates and hospital admission rates) is at a cluster level and collected from administrative data sources, the study will be less prone to social desirability bias. No consent for the primary outcome will be collected from the intervention and control building residents since it will be based on de-identified administrative data. Consent will only be collected from building residents who attend the CHAP sessions for their participation in the CHAP sessions.

Since the primary outcome is being analyzed at the building level, we anticipate no loss to follow-up for healthcare utilization data. We will retrospectively assess residents who lived in the intervention and control buildings at the pre- and post-intervention periods. There may be movement of residents in and out of the buildings; however, this will likely happen in both intervention and control buildings. This is expected to be balanced between the intervention and control arms. For the secondary outcome measures that require collection of data directly from residents, loss to follow-up is anticipated to be 40% [24]. A previous study conducted in this subsidized housing population found that there was a higher rate of deaths, relocations, and inability to contact in this population compared to the general population [21, 24]. However, we assume that losses to follow-up will be similar between the intervention and control groups.

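### Five imputations are too few for the 40% loss that the protocol itself expects, so EQ-5D-5L and QALY intervals and p-values would depend on the random seed

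*Protocol article*

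**What the plan says.** The protocol article, under Data analysis plan (Quantitative data), assigns the EQ-5D-5L and QALY outcomes to a GEE analysis: "For the secondary individual-level data (quality of life, QALY), we will use the intention-to-treat principle analysis". Missing follow-up values are handled by MCMC multiple imputation, which "with five imputations will be used if more than 5% of the participant outcome data is missing in the follow-up survey".

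Under Control of bias and loss to follow-up, the article says that for secondary outcomes needing data from residents "loss to follow-up is anticipated to be 40" percent. It adds, from an earlier study in subsidized housing, that "there was a higher rate of deaths, relocations, and inability to contact in this population" than in the general population. It does not say how the 40% divides among these reasons.

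Under Data collection, the EQ-5D-5L is given "to all residents of intervention buildings who attend a CHAP session", at two times: "when the participants attend their first CHAP session and then at the final CHAP session". Study aims describes the comparison as attendees against their own baseline.

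**The concern.** The number of imputations is fixed in the text, and so is the expected loss, and the two do not fit together. Five imputations serve well when missingness is just above the 5% trigger. At 40%, the pooled standard error is itself estimated from only five draws of the missing data. Two analysts using the same data and the same plan, but different seeds, could report visibly different intervals and p-values for two named secondary outcomes.

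A smaller matter lies alongside this. The imputation rule covers missing participant outcome data without distinction, and deaths are among the named reasons for loss. For QALYs, a living utility imputed after a death would credit time that was not lived. The comparison is before and after within attendees of intervention buildings, so no control arm would offset such an error.

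**Working it through.** **Inputs from the protocol article.** M = 5 imputations; trigger 5% missing; expected loss d = 0.40. The article derives neither the five nor the 40%, so there is no planned figure to reproduce first. Ratio of expected loss to trigger: 0.40 / 0.05 = 8.

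**Assumed: fraction of missing information, g.**
- If baseline carries no information, g = d = 0.40.
- If baseline predicts follow-up with correlation ρ, then for the change score g = x / (2(1 − ρ) + x), with x = (1 − ρ²)d / (1 − d).
- ρ = 0.5: x = 0.75 × 0.40/0.60 = 0.50; g = 0.50/1.50 = 0.333.
- ρ = 0.8: x = 0.36 × 0.40/0.60 = 0.24; g = 0.24/0.64 = 0.375.
- Range used: 0.33 to 0.40.

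**Formulas.**
- Monte Carlo error of the estimate, relative to its standard error: √(g/(M + 1)). The between-imputation variance is B = gT/(1 + 1/M), where T is the total variance, and the Monte Carlo variance is B/M = gT/(M + 1).
- Coefficient of variation (CV) of the standard error: g/√(2(M − 1)).
- Relative efficiency: 1/(1 + g/M).

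| | M = 5, g = 0.333 | M = 5, g = 0.40 | M = 40, g = 0.333 | M = 40, g = 0.40 |
|---|---|---|---|---|
| Monte Carlo error / SE | √(0.333/6) = 0.236 | √(0.40/6) = 0.258 | √(0.333/41) = 0.090 | √(0.40/41) = 0.099 |
| CV of SE | 0.333/√8 = 0.118 | 0.40/√8 = 0.141 | 0.333/√78 = 0.038 | 0.40/√78 = 0.045 |
| Relative efficiency | 0.938 | 0.926 | 0.992 | 0.990 |

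**Imputations needed for a CV of 5%:** M = 1 + 0.5(g/0.05)². For g = 0.333 this is 24 after rounding up; for g = 0.40 it is 33.

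**At the 5% trigger:** with g of 0.038 to 0.05, five imputations give a CV of 0.013 to 0.018. The choice suits the trigger, not the expected loss.

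**Simulation check.** Assumptions: 300 participants, ρ = 0.7, SD 0.2, 40% missing at random, no clustering. One data set was imputed and analysed 1,000 times.
- M = 5: the estimate varied by 0.27 of its SE, the CV of the SE was 0.15, and the 5th to 95th percentiles of p were 0.000006 to 0.018.
- M = 40: 0.10 of its SE, 0.04, and 0.00004 to 0.0005.

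**Deaths, as illustration only.** If a share p of attendees die and a utility u is imputed at 12 months instead of 0, a two-point linear QALY is too high by p × u/2. With assumed p of 2% to 8% and assumed u of 0.6 to 0.8, this runs from 0.02 × 0.6/2 = 0.006 to 0.08 × 0.8/2 = 0.032. None of these inputs is in the documents.

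**The case against.** Rubin's rules allow for a finite number of imputations, through the (1 + 1/M) term and a t reference distribution, so inference with five remains valid. The loss of efficiency is only about 6 to 7%, and a recorded seed makes a given result repeatable. All of that is correct. But efficiency describes average precision, and a recorded seed only freezes one draw. Neither stops the reported interval and p-value from depending on an arbitrary choice. In the simulation, p stayed below 0.05 between its 5th and 95th percentiles; the spread would matter more for a result near the threshold.

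Three stronger readings are tempting, and the article does not support them.

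- **That five imputations bias the results.** They do not; they add Monte Carlo noise.
- **That deaths will be imputed as living and so inflate quality of life.** The article neither says this nor rules it out. Such detail is commonly left to the full protocol or the statistical analysis plan. An upward error would arise for QALYs only if deaths were in fact imputed. For EQ-5D-5L change, whether death counts as zero is a choice of estimand.
- **That the imputation ignores clustering by building.** The article does not list the variables in the imputation model, so it shows neither inclusion nor omission.

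The reach is also limited. The primary outcome uses building-level administrative data. The cost-effectiveness analysis is described as building-level, based on administrative data and program costs.

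**Conclusion.** The point holds in a narrow form. At the protocol's own expected loss, five imputations leave a Monte Carlo error of about 0.24 to 0.26 of the standard error and a CV of the standard error of about 12 to 14%. With 40 imputations these fall to about 0.09 to 0.10 and about 4 to 4.5%. The result rests on a fraction of missing information of 0.33 to 0.40, which is inferred from the 40% loss and not stated. If the actual loss is much lower, the problem shrinks with it. It affects only the before-and-after EQ-5D-5L and QALY analyses among intervention attendees. On deaths, the finding is no more than a rule whose wording leaves the QALY treatment open. This is a worthwhile, nearly free improvement to secondary analyses, not a threat to the trial's main conclusion.

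**What to change.** Replace the fixed five with about 40 imputations, or one per percent of incomplete records if the loss turns out different. State that the imputation model includes the baseline EQ-5D-5L score and building, and record the seed. The cost is computing time.

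Add one sentence for QALYs: outcomes after a known death are not imputed as living values, utility is 0 from the date of death, and the number of known deaths is reported. This needs known deaths and their dates to be recorded. Some will stay unknown, because inability to contact is among the reasons for loss and the administrative data are de-identified. If the information has to be newly collected, that may be a protocol modification, and the Ethical approval section sends those to the ethics boards. The change in the number of imputations need not wait for it.

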#### Qualitative data

We will use a grounded theory approach. We will start with open coding followed by axial coding and theory generation to explain the process experience by participants as they attend the CHAP intervention.

#### Other analyses

We will conduct a quarterly process analysis in order to maintain trial fidelity (described earlier under Process evaluation measures). The main analyses will take place at the end of the trial. A subgroup analysis by gender is planned based on the data that we have available. Regression analysis will be used to determine if gender is a factor affecting our main outcomes.

### Control of bias and loss to follow-up

This will be an open trial with no blinding or masking. Due to the nature of the health intervention (health sessions in intervention buildings), it will not be possible to blind participants as to whether they are receiving the intervention or not. However, since randomization is at the building level and the primary outcome (ED visit rates and hospital admission rates) is at a cluster level and collected from administrative data sources, the study will be less prone to social desirability bias. No consent for the primary outcome will be collected from the intervention and control building residents since it will be based on de-identified administrative data. Consent will only be collected from building residents who attend the CHAP sessions for their participation in the CHAP sessions.

Since the primary outcome is being analyzed at the building level, we anticipate no loss to follow-up for healthcare utilization data. We will retrospectively assess residents who lived in the intervention and control buildings at the pre- and post-intervention periods. There may be movement of residents in and out of the buildings; however, this will likely happen in both intervention and control buildings. This is expected to be balanced between the intervention and control arms. For the secondary outcome measures that require collection of data directly from residents, loss to follow-up is anticipated to be 40% [24]. A previous study conducted in this subsidized housing population found that there was a higher rate of deaths, relocations, and inability to contact in this population compared to the general population [21, 24]. However, we assume that losses to follow-up will be similar between the intervention and control groups.

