### Study design

The trial will be an open-label, parallel, cluster RCT and is being reported according to the Standard Protocol Items: Recommendations for Interventional Trials (SPIRIT) checklist (see Additional file 1). Buildings will be the primary unit of analysis. It will be an open cohort study with repeated cross-sectional assessments comparing the outcomes of intervention and control buildings during the pre-intervention and 1-year post-intervention periods. See Fig. 1 for the study flowchart and Fig. 2 for the SPIRIT study schedule.

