### Allocation of intervention

Buildings will be organized into comparable pairs based on geographic, resource, and demographic characteristics. Each building pair will be allocated to receive or not receive the intervention (1:1 ratio) via computer-generated paired randomization by a statistician not affiliated with the project.

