## Data Availability

The datasets generated and/or analyzed during the current study are available from the corresponding author on reasonable request. The administrative dataset from this study is held securely in coded form. While data sharing agreements prohibit data holders from making the dataset publicly available, access may be granted to those who meet pre-specified criteria for confidential access. The full dataset creation plan and underlying analytic code are available from the authors upon request, understanding that the programs may rely upon coding templates or macros that are unique to the database holders.

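### The protocol rules out masking for everyone, but its reason covers only participants; it gives none for leaving outcome derivation and the primary analysis unmasked to arm

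*Protocol article*

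**What the plan says.** The Protocol article, Control of bias and loss to follow-up, is categorical: "This will be an open trial with no blinding or masking". The Study design section agrees: "The trial will be an open-label, parallel, cluster RCT". The reason offered is that "it will not be possible to blind participants as to whether they are receiving the intervention or not". The mitigation offered is that, with randomization by building and a cluster-level outcome from administrative sources, "the study will be less prone to social desirability bias".

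On the outcome itself, Data collection says: "The primary outcomes will be assessed using de-identified administrative datasets in Ontario and Quebec". The Quantitative data section says of health administrative data on residents: "It is possible to get this information in aggregate form for each building". The primary model is ANCOVA on building-level data, with pair as a fixed effect and baseline rate as covariate. Data Availability adds: "The full dataset creation plan and underlying analytic code are available from the authors upon request".

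Under Allocation of intervention, the sequence is produced "via computer-generated paired randomization by a statistician not affiliated with the project". That is the only role described as independent of the project, and it concerns allocation only.

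**The concern.** The statement is wider than its justification. Residents and those running the sessions plainly know which building has the programme. The people who turn administrative records into monthly building rates, and then fit the model, do not need to know it.

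Administrative data protect against residents reporting differently by arm. They do not protect against choices made while the outcome is being constructed by someone who knows which building in each pair had the programme. The Discussion part of the abstract anticipates a fall in CVD-related visits and admissions in the intervention buildings, so the team has a declared expectation. What is at stake is the credibility of the primary comparison if a choice made at derivation happens to favour the programme.

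**Working it through.** No figure in the plan depends on masking, so the check is a comparison of the sections.

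**1. Does the stated reason cover every role that the statement covers?**

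- Residents: covered. They see the sessions in their own building.
- Volunteers and the supervising research nurse (Intervention section): not named in the reason, but the same logic applies.
- Those who extract and derive the outcome, and those who fit the primary model: not covered. The mitigation is about social desirability, which also concerns residents' behaviour.

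**2. Could the last group be masked to arm in this design?**

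- The data are de-identified and administrative (Data collection), aggregated by building (Quantitative data) and assessed retrospectively (Control of bias and loss to follow-up).
- The outcome is produced from a dataset creation plan and code (Data Availability). Neither needs the arm as an input to compute a building's rate.
- The primary ANCOVA needs pair, baseline rate and a two-level arm variable. The levels can be coded labels.
- Inclusion requires a unique postal code per building (Inclusion and exclusion criteria). If extraction works by postal code, the extractor needs real building identifiers. That prevents hiding the building but not withholding the arm.

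**3. Is there anything left to choose?**

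| Element | Where | What is described |
|---|---|---|
| Which residents | Abstract, Methods/design | Those resident when the intervention starts |
| | Inclusion and exclusion criteria | Everyone living there in the pre- and post-intervention periods |
| | Control of bias and loss to follow-up | Those found retrospectively to have lived there at the two periods |
| Which window | Abstract, Methods/design | One year from randomization |
| | Primary and secondary outcome measures | One year before to one year after the intervention |
| | Data collection | The year before, and the year in which the programme runs |

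A group fixed at the start of the intervention is not the same as all residents over two periods in an open cohort. A year counted from randomization is not the same as the programme year if sessions start later. Naming ANCOVA in advance does not settle these choices, because they determine the rates that enter the model.

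**4. Result.** The reason fails to cover derivation and analysis, masking to arm is feasible there, and real discretion remains.

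**The case against.** The strongest reply has four parts.

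- **The sentence may be meant to describe trial conduct.** It sits in a paragraph about sessions and participants and matches the open-label description. The article does not say who derives or analyses the data, or that they know the allocation. A reader might infer that an unmasked analyst is part of the plan. The documents do not say so; it follows only from the breadth of the statement. What remains is that the article is not silent. It excludes masking without exception, so a fuller plan that masked the analyst would contradict it.
- **The exposure is narrow and has a more direct remedy.** Events are recorded in routine data outside the trial and the model is named. Reconciling the resident and window definitions would close much of the gap. This stands and limits the severity. Masking would still cover derivation choices that no definition anticipates.
- **Masking is not free.** Extraction may need postal codes, two provinces' datasets are involved, and programme costs enter a building-level analysis. This also stands, and it is why only the arm need be withheld at extraction.
- **No size can be attached.** A reader might be tempted to quote an error rate of about 8–11% instead of 5%. That comes from assuming 2 to 4 versions of the outcome, correlated 0.8, and keeping the most extreme in either direction. Such selection needs no knowledge of arm, and coded labels would not prevent it. Under the same assumptions, always keeping the version most favourable to the programme gives a two-sided error of 5.0%, 5.6% and 6.2% for 2, 3 and 4 versions, and false claims of benefit of 3.9%, 4.9% and 5.7% instead of 2.5%. Neither the number of versions nor the correlation is in the article, so none of these figures measures the bias in this trial.

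**Conclusion.** The point holds in a limited form. The article excludes masking for every role but gives a reason that reaches only participants and, by extension, those delivering the sessions. It gives no reason why the people deriving and analysing the retrospective, building-level outcome could not be masked to arm, although it leaves open which residents and which window count.

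The size of any bias cannot be estimated from the document. The conclusion assumes that the no-masking sentence means what it says for all roles, and that outcome derivation does not need the arm, which the described data sources support. It does not imply that anyone has made or will make biased choices, or that the administrative outcome is unsound. It is a cheap improvement.

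**What to change.** In Control of bias and loss to follow-up, limit the no-masking statement to participants and programme staff. Then add wording such as: *Those deriving the primary outcome from the administrative data will not be given arm assignments. The primary analysis will use coded arm labels. The unaffiliated statistician who generated the allocation will hold the key until the analysis dataset and the primary model output are final.* Building identifiers such as postal codes may still be used for extraction; only the arm is withheld there. If masking is not possible in one of the provinces, say so and give the reason.

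The cost is a revised statement, a coded arm variable, and an agreement with the statistician to hold the key. The downside is one of timing: programme cost and attendance data reveal the arm, so they can be linked only after the primary analysis is locked. Sample size, model and procedures for residents do not change. The resident and window definitions should be reconciled as well, since masking does not replace that.
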